**Protocol #: 17-0920**

**Project Title: Vets Sleep**

**Principal Investigator: [name].**

**Version Date: 10-18-18**

**I**. **Hypotheses and Specific Aims**:

**Specific Aim**: Determine the efficacy of a prominent computerized cognitive behavioral therapy (cCBT), called Sleep Healthy Using the Internet (SHUTi), for treatment of insomnia among Operation Enduring Freedom (OEF), Operation Iraqi Freedom (OIF), and Operation New Dawn (OND) Veterans. Efficacy will be evaluated using a two group (SHUTi vs. educational website control) longitudinal (four time points) randomized controlled trial (RCT) design.

*Objective 1.1*: Determine if there are significant differences in insomnia symptom reduction and physical and mental health functioning between participants in the two groups.

*Hypothesis 1.1*: Participants randomized to SHUTi will report a significant pre-intervention to post-intervention decrease in insomnia symptoms, and improvement in functioning compared to participants who are randomized to the educational website control.

*Objective 1.2 & 1.3*: Determine whether changes in insomnia symptoms and physical and mental health functioning are maintained six-months and one-year post-intervention.

*Hypothesis 1.2 & 1.3*: Participants randomized to SHUTi will report a significant pre-intervention to six-months and one-year post-intervention decrease in insomnia symptoms, and improvement in functioning compared to participants who are randomized to the educational website control.

*Exploratory Objective 1.4*: Determine whether SHUTi is associated with significant reductions in sleep diary parameters (i.e., sleep efficiency, sleep onset latency, wake after sleep onset) and key variables including suicidal ideation, depressive symptoms, anxiety, and post-traumatic stress disorder (PTSD)).

**II**. **Background and Significance**:

Chronic sleep problems are a major complaint among OEF/OIF/OND Veterans, with rates of insomnia dramatically increasing over the past decade [49-51]. Elevated rates of insomnia are especially concerning given that insomnia may precede functionally impairing symptoms of depressive episodes, post-traumatic responses, and self-directed violence (SDV) [2,52,53]. Furthermore, even after resolution of comorbid symptoms, insomnia symptoms often remain at clinical levels, and continue to impact functioning [54]. Thus, it is imperative that individuals suffering from insomnia receive evidence-based therapies (EBT) that reduce insomnia and associated comorbid symptoms, improve quality of life, and increase function.

Despite the high prevalence of insomnia, only a small percentage of individuals with insomnia actually receive any type of treatment for their symptoms [55]. Cognitive Behavioral Therapy for Insomnia (CBT-I) has quickly emerged as one of the most efficacious treatments for insomnia. In 2005, the National Institutes of Health (NIH) State-of-the-Science conference on insomnia identified CBT-I as a first-line treatment given that CBT-I was found to be as effective as prescription medications for the short-term treatment of insomnia. Consequently, CBT-I has emerged as the “treatment of choice” for managing sleep/wake complaints [15], with evidence suggesting that 70-80% of individuals obtain benefit from the intervention [56]. The efficacy of CBT-I has been established in numerous studies and outlined in three meta-analyses [56-59].

Despite the widespread data in support of CBT-I, many VA facilitates do not have sufficient access to trained CBT-I providers. Due to lack of access to trained clinicians, coupled with the increasing demand for services from returning OEF/OIF/OND Veterans, the need for evidenced-based sleep interventions will continue to intensify. Thus, despite the VA’s efforts to disseminate CBT-I, there remains a necessity to expand access to CBT-I above and beyond what can be delivered by CBT-I trained providers. Evidence for the positive effects of CBT-I, along with access issues, suggests the need to incorporate innovative methods, such as cCBTs, for delivery of CBT-I. Existing web-based cCBTs offer a potentially efficacious means of delivering insomnia treatments by providing the opportunity to engage in an EBTs via computers. From both a policy and clinical perspective, cCBTs have garnered attention due to their potential to overcome barriers to treatment, including cost, scheduling and travel demands, stigma, and lack of trained EBT clinicians [25]. Furthermore, leveraging technology to meet treatment demands is consistent with service delivery models based upon stepped care principles [60].

The SHUTi program is based upon the CBT-I model, consisting of the same behavioral, educational, and cognitive treatment components underlying CBT-I and has been found to be efficacious for the treatment of insomnia [40-44]. In the first SHUTi pilot trial [40], 44 civilian adults with primary insomnia were randomly assigned to either SHUTi or a wait-list control group. Prospectively collected sleep diary data showed significant improvements for SHUTi users in sleep efficiency, nighttime awakenings, and total sleep time; whereas the control group showed no significant changes. SHUTi participants also showed clinical improvement in insomnia severity, with 73% of SHUTi users falling into the “no insomnia” category after treatment; no control participants met this criterion. Positive gains were also maintained for SHUTi participants at six months. In addition, although SHUTi was not specifically designed to target comorbid symptoms, significant improvements were found in mood (e.g., depressive and anxious affect), overall health (e.g., fatigue), and quality of life [41]. A recent RCT by Christensen and colleagues, demonstrated that SHUTi, compared to an Internet-based placebo control group, was significantly associated with lower depression symptoms at six-weeks and six-months compared to the control group in a sample of Australian Internet users with insomnia and depression symptoms that did not meet criteria for major depressive disorder [61]. In sum, data from several rigorous clinical trials, including a variety of civilian patient groups, consistently show significant and clinically meaningful improvements in sleep outcomes and co-occurring symptoms with SHUTi.

Despite the growing evidence base for SHUTi, no RCT of SHUTi has been conducted with Veterans or military personnel. Research demonstrating the efficacy of SHUTi among military and Veteran populations is essential to meeting treatment demands and improving the health of Veterans. Given empirical evidence supporting the association between insomnia and comorbid conditions, SHUTi may offer an invaluable resource to address the needs of Veterans and the Veterans Health Administration (VHA).

**III**. **Preliminary Studies/Progress Report:**

As noted above, several researchers have provided efficacy data supporting SHUTi as a treatment intervention that is associated with reductions in insomnia and comorbid symptoms, yet no RCT of SHUTi has been conducted within a Veteran population. No prior research on SHUTi has been conducted by this team at the ECHCS.

**IV. Research** **Methods**

**A. Outcome Measure(s):**

***Screening Measure:***

*Screening Form:* A screening form will be used to assist in the assessment of eligibility criteria (e.g., OEF/OIF/OND Veteran, eligible to receive care at DVAMC, insomnia diagnosis).

***Primary Outcome Measure:***

*Insomnia Severity Index (ISI)* [46]*.* The ISI is a seven-item index of subjective sleep difficulty. Respondents provide information on difficulty with sleep onset, sleep maintenance, and early morning awakenings, as well as interferences with daytime functioning, how noticeable sleep problems are to others, distress caused by problematic sleep, and overall sleep satisfaction. Total scores range from 0 to 28 with higher scores indicating greater insomnia severity. The ISI is a reliable, valid measure that can be delivered through the Internet [62] and is sensitive to changes in insomnia treatment studies [46]. The suggested guidelines for interpretation are: 0-7 = no clinically significant insomnia; 8-14 = subthreshold insomnia; 15-21 = clinical insomnia of moderate severity; 22-28 = severe clinical insomnia.

***Secondary Outcome Measure:***

*The Veteran’s SF-36 (VA SF-36)* [63]: The VA SF-36 is the primary measure of health-related quality of life used within VA populations, built on the Medical Outcomes Study (MOS) SF-36 [64]. The Veteran’s SF-36 measures eight concepts of health, with two summary scores: physical component summary and mental component summary.

***Additional Measures:***

*Adult Suicidal Ideation Questionnaire (ASIQ)* [47]. The ASIQ is a 25-item self-report instrument designed to estimate a respondent’s current level of suicidal ideation. Each ASIQ item is rated on a 7-point scale indicating the frequency of each item over the past month. The ASIQ has high internal consistency and test-retest reliability in clinical and nonclinical samples [65].

*Beck Anxiety Inventory (BAI)* [48]. The BAI is a 21-item, self-report rating inventory that measures subjective, somatic, and panic-related symptoms of anxiety.

*Beck Depression Inventory II (BDI-II)* [66]. The BDI-II is a 21-item, self-report rating inventory that measures characteristic attitudes and symptoms of depression.

*Follow-Up Questions:* During the follow-up assessments, all participants will be asked about whether they have made any changes to sleep medications and sought sleep treatment in addition to brief inquiries about demographic changes (i.e., marital status, employment status, student status, current homelessness). Participants that received SHUTi will be asked four brief open-ended questions designed to collect qualitative information on how participation in SHUTi has affected the participant, the most helpful aspect of participating, and ways to improve SHUTi.

*Internet Evaluation and Utility Questionnaire* [43]: The Internet Evaluation and Utility Questionnaire measures participants’ experiences and perceptions of an Internet intervention. The constructs measured include items on ease of use, convenience, engagement, enjoyment, layout, privacy, satisfaction, and acceptability. Additional items assess perceptions of web program material in terms of usefulness, comprehension, credibility, likelihood of returning, mode of delivery, and helpfulness.

*Internet Impact and Effectiveness Questionnaire* [43]: The Internet Impact and Effectiveness Questionnaire measures participants’ perceptions of an Internet intervention in terms of the program’s effectiveness in resolving their targeted health condition. Perceived impact is measured in terms of helpfulness, knowledge gains, treatment effectiveness for self and others, long-term effectiveness, quality of life, mood, physical activity, family and peer relationships, social activity, school/work attendance and performance, treatment implementation, goal-orientation, confidence in ability to manage condition, relapse prevention, and service reduction.

*Life Experiences Survey (LES):* Based upon the Holmes-Rahe Life Change Index Scale [67], the LES queries participants about a variety of life events (e.g., death of a close friend, loss of child). Participants will be asked to indicate yes or no as to whether any of these life events have occurred since the last study assessment as a way to characterize major life events that may be associated with long-term changes in sleep patterns.

*Military Suicide Research Consortium (MSRC) Common Data Elements (CDE).* The MSRC CDE is a composite measure of several items taken from commonly utilized self-report assessments. The CDE are required to be administered to all participants by the funding agency.

*Military Suicide Research Consortium (MSRC) Demographics:* Required by the funding agency, this demographics form will collect information (e.g., gender, race, education, military history) to describe key demographic and military participant characteristics.

*Morningness/Eveningness Questionnaire (MEQ)* [68]: The MEQ is a 19-item self-report instrument designed to assess an individual’s chronotype: evening, intermediate, or morning. Information about participant chronotype will help determine whether certain chronotypes may be more or less sensitive to conventional insomnia treatment.

*Posttraumatic Stress Disorder Checklist for DSM-5 (PCL-5)* [69]. The PCL-5 is a psychometrically sound self-report measure that assesses the severity of PTSD symptoms in the past month.

*Sleep Diary* [70]. A Sleep Diary includes assessment of 10 standard sleep parameters: time to fall asleep; number and length of awakenings at night; time of awakening and arising from bed in the morning; length of naps; subjective sense of how refreshed the participant felt upon awakening as well as how sound they sleep during the night; and amount of medication and alcohol used as a sleep aid. Data suggest that sleep diary assessments are a valid and reliable way to collect information on sleep parameters. They have also been found to provide a more comprehensive understanding of sleep patterns than can be achieved using objective measures of sleep, such as polysomnography, which is typically administered for one to two nights only [71]. Sleep diaries will provide information on over the counter and prescribed sleep medication use.

*Revised Narrative Evaluation of Intervention Interview (NEII)* [72]: The NEII, slightly revised by this study team to be applicable to SHUTi, is an assessment tool designed to help participants evaluate and describe the process and outcome of an intervention. This qualitative feedback will be used to inform future implementation efforts.

*Revised Reasons for Termination Questionnaire* [73]: The Reasons for Termination Questionnaire, slightly revised by this study team to be applicable to SHUTi, asks participants to indicate reasons why (e.g., time problems, problems improved and no longer felt a need for intervention) they stopped participating in the intervention. Participants are then asked to rate the amount of influence each reason had on the decision to stop participating.

**Table S1.** Measures, time to completion, and purpose of study measures.

| **Measure** | **Time** | **Purpose** |
| --- | --- | --- |
| **Phone Screening** | | |
| Screening Form | 5-20 | Determine eligibility for the study |
| **Baseline Assessment (Time 1): 100 minutes** | | |
| Insomnia Severity Index (ISI) | 5 | Assess insomnia symptoms |
| Veteran’s SF-36 | 15 | Assess health-related quality of life |
| MSRC Demographics | 5 | Collect participant demographics |
| Adult Suicidal Ideation Questionnaire (ASIQ) | 10 | Assess past-month suicidal ideation |
| PCL-5 | 5 | Assess PTSD symptoms |
| Beck Depression Inventory-II (BDI-II) | 5 | Assess depressive symptoms |
| Beck Anxiety Inventory (BAI) | 5 | Assess anxiety symptoms |
| Morningness/Eveningness Questionnaire | 10 | Assess factors impacting circadian rhythm |
| MSRC Common Data Elements | 40 | Study sponsor measure – abbreviated self-report items |
| **Post-Intervention Assessment (Time 2): 85-120 minutes** | | |
| Insomnia Severity Index (ISI) | 5 | Assess insomnia symptoms |
| Veteran’s SF-36 | 15 | Assess health-related quality of life |
| Adult Suicidal Ideation Questionnaire (ASIQ) | 10 | Assess past-month suicidal ideation |
| PCL-5 | 5 | Assess PTSD symptoms |
| Beck Depression Inventory-II (BDI-II) | 5 | Assess depressive symptoms |
| Beck Anxiety Inventory (BAI) | 5 | Assess anxiety symptoms |
| Revised Reasons for Termination Questionnaire | 5* | Assess reasons for non-completion of SHUTi |
| Revised NEII | 15** | Qualitative feedback designed to inform future implementation efforts |
| Internet Evaluation and Utility Questionnaire | 5** | Feedback on experiences and perceptions of SHUTi |
| Internet Impact and Effectiveness Questionnaire | 10** | Feedback on perceptions of SHUTi’s effectiveness |
| MSRC Common Data Elements | 40 | Study sponsor measure – abbreviated self-report items |
| **6-Month Follow-Up Post-Intervention Assessment (Time 3): 95-100 minutes** | | |
| Insomnia Severity Index (ISI) | 5 | Assess insomnia symptoms |
| Veteran’s SF-36 | 15 | Assess health-related quality of life |
| Adult Suicidal Ideation Questionnaire (ASIQ) | 10 | Assess past-month suicidal ideation |
| PCL-5 | 5 | Assess PTSD symptoms |
| Beck Depression Inventory-II (BDI-II) | 5 | Assess depressive symptoms |
| Beck Anxiety Inventory (BAI) | 5 | Assess anxiety symptoms |
| Follow-Up Questions – SHUTi | 5** | Feedback on experiences and perceptions of SHUTi |
| Follow-Up Questions – Sleep and Demographics | 5 | Information on changes in sleep medication/treatment and demographics |
| Life Experiences Survey | 5 | Information on life changes since last assessment |
| MSRC Common Data Elements | 40 | Study sponsor measure – abbreviated self-report items |
| **1-Year Follow-Up Post-Intervention Assessment (Time 4): 95-100 minutes** | | |
| Insomnia Severity Index (ISI) | 5 | Assess insomnia symptoms |
| Veteran’s SF-36 | 15 | Assess health-related quality of life |
| Adult Suicidal Ideation Questionnaire (ASIQ) | 10 | Assess past-month suicidal ideation |
| PCL-5 | 5 | Assess PTSD symptoms |
| Beck Depression Inventory-II (BDI-II) | 5 | Assess depressive symptoms |
| Beck Anxiety Inventory (BAI) | 5 | Assess anxiety symptoms |
| Follow-Up Questions – SHUTi | 5** | Feedback on experiences and perceptions of SHUTi |
| Follow-Up Questions – Sleep and Demographics | 5 | Information on changes in sleep medication/treatment and demographics |
| Life Experiences Survey | 5 | Information on life changes since last assessment |
| MSRC Common Data Elements | 40 | Study sponsor measure – abbreviated self-report items |

*Assessment administered only to participants randomized to SHUTi that did not complete all 6 cores. **Assessments administered only to participants randomized to SHUTi.

Note: Sleep diaries will be completed two weeks before baseline assessment (Time 1) and during the two weeks after post-intervention assessment (Time 2). Participants will also complete the ISI and sleep diaries throughout the intervention. If a SHUTi participant contacts the study team indicating that they would like to withdraw from the study, the participant will have the opportunity, if willing, to provide responses to the Revised Reasons for Termination Questionnaire, via phone.

1. **Description of Population to be Enrolled:**

Participants will be recruited from populations of Veterans receiving or eligible to receive physical and mental health care within the VA Eastern Colorado Health Care System (ECHCS). We will enroll up to 250 eligible Veterans who meet the study inclusion/exclusion criteria described below.

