***Analysis Plan***

All analyses will assume a two-sided test of hypothesis and a significance level of 0.05, unless otherwise noted. Preliminary descriptive and graphical analyses (e.g., boxplots, scatterplots) will be used for data checking and visualization. Demographic and clinical characteristics (including but not limited to age, gender, PTSD, BDI-II scores, BAI scores, and the Life Experiences Survey for the six-month and one-year outcomes) will be compared between groups using t-tests, chi-square tests, Wilcoxon rank-sum tests or Fisher’s exact tests as appropriate to check randomization. Any variable that is found to be different between the groups at the p<0.10 level, and is a plausible potential confounder in consideration of the association under investigation, will be included as a covariate in the analyses described below. This includes an examination as to whether suicide risk variables will be included as covariates.

Given that the aim of the RCT is to test the efficacy of SHUTi, we will perform a per-protocol analysis such that those participants who do not have post-intervention data will not be included in the analysis. Additionally, we will perform a sensitivity analysis using the last value carried forward for those who drop out. This conservative contrast will give some insight into the effectiveness of the intervention and bolster the efficacy findings if they are consistent with the primary analysis.

Primary Aim, Hypothesis 1.1. The primary analyses will be the comparison between groups of the change in 1) insomnia symptom severity as measured by the ISI, 2) physical health as measured by the physical component of the Veteran’s SF-36, and 3) mental health as measured by the mental component summary score on the Veteran’s SF-36, from Time 1 to Time 2. Statistical inference regarding the difference between intervention groups will be based on the estimated coefficient for a group indicator variable in each of three analysis of covariance models with the change from Time 1 to Time 2 for each outcome serving as the dependent variable. Additional covariates will include the baseline value of the outcome to improve precision of the estimate, and any potential confounders discovered in the randomization check. To control for the three primary comparisons, the significance level will be set to 0.0167.

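### Time 2 takes 85 minutes for control and 115 to 120 for SHUTi, and the protocol gives no short route to the 5-minute ISI for people who decline or withdraw

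*Protocol*

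**What the plan says.** Protocol section IV.A, Table S1, lists the forms and times for each assessment. The post-intervention block is headed "Post-Intervention Assessment (Time 2): 85-120 minutes". It opens with the primary outcome ("Insomnia Severity Index (ISI) | 5 | Assess insomnia symptoms"), followed by the Veteran's SF-36 ("SF-36 | 15 | Assess health-related quality of life").

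Three feedback forms go to all SHUTi participants and to no one in control. A fourth, the termination questionnaire, carries the footnote "Assessment administered only to participants randomized to SHUTi that did not complete all 6 cores". All four stand before the MSRC Common Data Elements, which close the block.

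The note under Table S1 covers withdrawal. A SHUTi participant who contacts the team to withdraw may answer the termination questionnaire by phone. The note asks for no outcome measure at that contact and describes no such contact for control.

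Under Assessment & Intervention Procedures, all allocated participants are contacted, reminded by phone or email, and paid $50 for Time 2. The battery is completed online.

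Under Analysis Plan, "those participants who do not have post-intervention data will not be included in the analysis". Last value carried forward is a sensitivity analysis, and so is a mixed-effects model on all available data. A hypothesis whose mixed-model result disagrees is to be called inconclusive.

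**The concern.** The primary analyses use the change from Time 1 to Time 2, and people without Time 2 data drop out of them. Whatever makes Time 2 harder to complete therefore bears directly on the primary comparison. The visit is longer in one arm only, and the added time collects feedback on SHUTi or reasons for not finishing it, none of which is needed for Hypothesis 1.1.

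For a person unwilling to sit through the whole session, the protocol offers nothing shorter. Where it does provide a brief phone contact, it spends those 5 minutes on the termination form and not on the ISI, which takes the same time. If the people lost differ between arms, the retained groups are no longer comparable as randomised, and analysis can repair that only under assumptions about the missing values.

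**Working it through.** **1. Reproduce the stated range from the Table S1 item times.**

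- Common forms: ISI 5, SF-36 15, ASIQ 10, PCL-5 5, BDI-II 5, BAI 5, Common Data Elements 40.
- Control: 5 + 15 + 10 + 5 + 5 + 5 + 40 = 85 minutes.
- SHUTi, all cores done: 85 + 15 (NEII) + 5 + 10 (the two Internet questionnaires) = 115 minutes.
- SHUTi, not all cores done: 115 + 5 (termination questionnaire) = 120 minutes.

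This matches the stated 85 to 120 minutes exactly.

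**2. Express the difference.**

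- Against the control session: 115/85 = 1.353 (+35%) and 120/85 = 1.412 (+41%).
- Against the 100-minute baseline that everyone randomised has already completed: +15% and +20%.
- Against the other visits: Time 1 is 100 minutes in both arms, and Times 3 and 4 are 95 for control and 100 for SHUTi (+5%). The large imbalance is confined to Time 2.
- The flat $50 works out at 50/85 × 60 = $35.3 per hour for control, and $26.1 and $25.0 for the two SHUTi groups.

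**3. Compare with what a fallback would take.** The ISI alone takes 5 minutes, which is 5/85 = 5.9% of the control session and 5/120 = 4.2% of the longest SHUTi session. The ISI plus SF-36 takes 5 + 15 = 20 minutes and covers all three primary comparisons.

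**4. Set the provisions side by side.** The withdrawal note gives a phone route for the termination form only. The post-intervention procedure gives reminders and online completion of the full battery. The analysis plan removes those without Time 2 data. None of the three supplies a shortened assessment. The ISI is also collected during the intervention, but it is not named as a substitute for the Time 2 value.

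**5. Illustrate the possible size (all inputs assumed).** Let a fraction *l* of an arm be lost, and let those lost have change scores worse by *g* SD than those retained. The full-arm mean is then the retained mean minus *l* × *g*, so the retained mean is too favourable by *l* × *g*. With the same *g* in both arms, the between-arm contrast shifts by (*l* SHUTi − *l* control) × *g*.

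- Loss 20% control, 30% SHUTi (113 × 0.80 ≈ 90 and 113 × 0.70 ≈ 79 analysed): 0.10 × 0.25 = 0.025 SD, up to 0.10 × 0.5 = 0.05 SD.
- Loss 15% control, 35% SHUTi (about 96 and 73 analysed): 0.20 × 0.25 = 0.05 SD, up to 0.20 × 0.5 = 0.10 SD.

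If those lost did better than those retained, the sign reverses. For scale, the design effect is 0.6 SD, so 0.10 SD would be about one sixth of it. The protocol assumes 25% attrition overall and gives no split by arm, so these figures show a range and are not estimates.

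**The case against.** The strongest reply is that nothing here is an error. Table S1 states the range openly and footnotes who gets which form. The ISI and SF-36 are already listed first, so if that is the order of completion, the extra minutes come after the outcomes that matter. Everyone is contacted and reminded, everyone has already managed a 100-minute baseline, and the protocol cites 0 to 12% pre-to-post attrition in earlier SHUTi trials. Two sensitivity analyses are planned, and the mixed model can turn a finding into an inconclusive one.

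Much of this stands. Three stronger readings are tempting, and the protocol does not support them:

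- *That the SHUTi effect will be overstated.* A reader might infer that people who stop SHUTi have improved less. Yet the protocol's description of the termination questionnaire gives improvement of the problem as one example reason for stopping. The direction is open, and no arm-specific loss is given.
- *That an ISI is thrown away when the rest of the battery is unfinished.* The exclusion rule speaks of lacking post-intervention data. It does not require a complete battery, and each outcome has its own model.
- *That those who stopped treatment carry a much heavier load.* Their excess over other SHUTi participants is one 5-minute form (120 against 115), and the footnote covers anyone short of six cores, including slow users.

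The reply does not remove the missing fallback. Listing the ISI first does not help someone who declines to start a session of up to two hours, or who withdraws. Carrying a last value forward substitutes an earlier observation for an unobserved one, and the mixed model relies on the observed data explaining the missingness. Neither replaces a 5-minute questionnaire that could have been requested.

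**Conclusion.** The point holds as a low-cost improvement to data collection; it does not show that the trial is biased. The firm parts come straight from Table S1 and the text: 85 minutes against 115 to 120, SHUTi-only forms listed ahead of the 40-minute common data elements, a withdrawal contact that omits the ISI, no short route in either arm, and exclusion from the primary analysis when Time 2 data are absent. Together they create a risk of avoidable, possibly arm-related, loss of the primary outcome.

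The size and direction of any resulting bias cannot be derived from the protocol. The 0.025 to 0.10 SD illustration rests wholly on assumed losses and an assumed common gap, and could take either sign. The risk is smaller if forms are completed in the listed order and saved one by one, but the protocol states neither.

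**What to change.** Amend Table S1, its withdrawal note and the follow-up procedures in two respects.

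1. **Fallback in both arms at Times 2, 3 and 4.** Offer the ISI plus SF-36 (20 minutes), or failing that the ISI alone (5 minutes), to anyone who declines the full battery, has not completed it after reminders, or withdraws but agrees to give data. Collect it online or in the phone contact the withdrawal note already allows, extended to control. State that these responses count as data for that time point. Do not offer the short form up front merely because someone stopped using the website; the full battery, including the funder-required elements, should remain the default.
2. **Order of forms.** State that the ISI and SF-36 come first. Have the SHUTi-only forms open automatically online once the common 85-minute battery is submitted. The blinded assessor should not chase them, since a reminder about a SHUTi-only form would reveal allocation.

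The cost is an amendment and a reordering of web forms, with no extra staff. Somewhat fewer SHUTi feedback forms will come back. Fallback participants will lack the secondary measures and the common data elements, and those giving only the ISI will also lack the SF-36 scores, which are two of the three primary comparisons. That is why the ISI plus SF-36 should be offered first.
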